**2. Research Objective**

This study will use the China Health and Physical Education Curriculum Model for 12 weeks of physical education teaching. Relevant physical health and psychological health indicators will be tested before and after the teaching. Changes in metabolites before and after the teaching will be detected through non-targeted metabolomics technology. The study will analyze the effects and metabolic mechanisms of one-time and long-term teaching using the China Health and Physical Education Curriculum Model on improving students' physical and mental health levels, aiming to provide new insights into improving students' physical and mental health through this model.

1. **Research Methodology**

- 1. Participants and Grouping

The sample size was calculated using G*Power software, selecting “Means: Difference between two independent means (two groups)” under “t tests.” The assumptions included a medium effect size of 0.5, an α error probability of 0.05, and a power (1 - β error probability) of 0.80, with equal sample sizes in both groups. The minimum required sample size for the study was calculated to be 64.

This study employed a randomized controlled trial design. Six classes of the same grade were randomly selected, with three assigned to the experimental group and the other three to the control group. The researchers wrote the allocation information for each participating class (e.g., experimental or control group) on slips of paper and placed these slips into envelopes. Each envelope contained the random allocation information for the respective class. Both the participants and their parents in the two groups were introduced to the content of the experiment and the precautions during the experimental process to ensure they had a detailed understanding. After obtaining the opinions of the student participants and their parents based on the inclusion and exclusion criteria, informed consent forms were signed.

3.2 Inclusion Criteria, Exclusion Criteria, Criteria for Removal, and Mid-study Withdrawal Criteria

Inclusion criteria: (1) Primary and secondary school students; (2) Able to complete the 12-week intervention and the three tests before the intervention, after the first intervention, and after 12 weeks of intervention.

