Exclusion criteria: (1) Students with contraindications to physical activity; (2) Students with severe cardiovascular or musculoskeletal diseases; (3) Students who are sick, injured, have chronic diseases, are taking medication, or are in their menstrual period (female students); (4) Students who have not signed the informed consent form.

Criteria for removal: (1) Students absent for more than one-third of the sessions; (2) Students who are unable to complete the tests due to personal or family reasons; (3) Students who participated in other sports training sessions during the intervention, violating the intervention plan.

Mid-study withdrawal criteria: Students who transferred schools or could not continue participating in the study due to other reasons.

3.3Experiment Content

This study was primarily conducted in primary and secondary schools, involving six classes (approximately 300 students) who voluntarily participated. Three classes were designated as experimental groups, which adopted the Healthy Physical Education Curriculum Model of China for physical education instruction, while the other three classes served as control groups, receiving traditional physical education instruction.

The experimental groups underwent 12 weeks of physical education instruction based on the Healthy Physical Education Curriculum Model of China, whereas the control groups followed the conventional traditional physical education instruction for the same duration. Pre- and post-instruction assessments were conducted to measure the students' physical and mental health indicators. The physical health indicators were evaluated according to the National Student Physical Health Standard (Revised in 2014), which included anthropometric measurements, vital capacity, speed, strength, flexibility, agility, and other indicators. The mental health indicators were assessed through questionnaires, covering healthy behaviors, sportsmanship, depressive symptoms, and other indicators. Additionally, 40 students (20 from the experimental group and 20 from the control group) were randomly selected to provide 15 ml of urine samples before instruction, after the first session of instruction, and after 12 weeks of instruction. Non-targeted metabolomics techniques were employed to detect changes in metabolites within the body, in order to explore the underlying mechanisms by which exercise promotes health.

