3.5 Experimental Procedure

Informing the research process and precautions—Grouping by class—Pre-instruction testing (including physical health indicators, mental health indicators, and metabolite collection)—Testing after the first session of instruction (metabolite collection only)—Conducting 12 weeks of physical education instruction (experimental groups adopting the Chinese Healthy Physical Education Curriculum Model, control groups adopting traditional physical education instruction)—Post-instruction testing (consistent with pre-instruction testing).

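### The protocol gives two conflicting orders for informing and allocation, and neither secures consent and screening before a class's arm is known, so recruitment bias cannot be excluded

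*Protocol*

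**What the plan says.** The first part of Research Methodology, Participants and Grouping (3.1 by its position before 3.2), gives this sequence:

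- Allocation: "Six classes of the same grade were randomly selected, with three assigned to the experimental group and the other three to the control group".
- Mechanism: the researchers put slips in envelopes, and "Each envelope contained the random allocation information for the respective class". Nothing is said about sealing, time of opening or who opens them.
- Informing: "Both the participants and their parents in the two groups were introduced to the content of the experiment and the precautions during the experimental process".
- Eligibility and consent, as the last step: "After obtaining the opinions of the student participants and their parents based on the inclusion and exclusion criteria, informed consent forms were signed".

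Section 3.5, the procedural sequence, begins differently: "Informing the research process and precautions—Grouping by class—Pre-instruction testing". It mentions neither eligibility review nor consent.

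Entry is decided student by student. Section 3.2 excludes "Students who have not signed the informed consent form", and one of its inclusion criteria looks forward: "Able to complete the 12-week intervention and the three tests before the intervention, after the first intervention, and after 12 weeks of intervention". Section 3.3 describes participation as voluntary, with about 300 students in the six classes.

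**The concern.** When classes are randomised and students consent individually, randomisation balances the classes in expectation. It does not balance the students who agree to join unless they are identified before the arm is known. If families know the arm, willingness to join may depend on it. If staff know the arm, so may their view of who can complete the programme. The experimental lessons carry a specified load (Table 1: exercise density above 75%, 140-160 beats/min). No such load is set for the control lessons, so a reluctant or unfit student could decide, or be judged, differently in the two arms.

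At stake is whether the student-level comparison keeps the protection of randomisation. Bias that enters at recruitment cannot be reliably removed in the analysis, and section 3.10 plans only unadjusted t-tests.

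**Working it through.** **1. The two orders side by side**

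| Step | Participants and Grouping | Section 3.5 |
|---|---|---|
| Classes allocated | first | second |
| Families informed | second | first |
| Eligibility reviewed | third | not placed |
| Consent signed | third | not placed |
| Baseline testing | not placed | third |

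The sections disagree on the first two steps. Under the first order, screening and consent follow allocation. Under the second, they could fall before or after it. Neither order guarantees that enrolment is closed before the arm is known.

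**2. What the planned test does with a selection effect**

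I read section 3.10 as an independent t-test on each student's post-minus-pre difference, alongside a comparison of the arms at baseline. Suppose selective entry shifts an arm's mean by b at baseline and c at follow-up. The bias in the change comparison is c − b. If the shift is a stable level difference, c = b and the bias is zero. If the selecting trait, such as motivation, also affects improvement, c differs from b and the bias stays.

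**3. Illustration of size, on assumed inputs**

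The documents give no consent rates, so the protocol has no figure to reproduce here. Assume willingness to join is standard normal and the least willing fraction p of an arm declines. The mean willingness of those who stay rises by φ(z_p)/(1 − p):

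- p = 0.05: 0.1031/0.95 = 0.109
- p = 0.10: 0.1755/0.90 = 0.195
- p = 0.20: 0.2800/0.80 = 0.350
- p = 0.30: 0.3477/0.70 = 0.497

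The spurious arm difference in the compared outcome is r times the difference between the arms' shifts. Here r is the assumed correlation of willingness with that outcome.

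| Consent in the two arms | Difference in shift | r = 0.1 | r = 0.3 | r = 0.5 |
|---|---|---|---|---|
| 95% and 90% | 0.086 | 0.01 | 0.03 | 0.04 |
| 95% and 80% | 0.241 | 0.02 | 0.07 | 0.12 |
| 90% and 70% | 0.302 | 0.03 | 0.09 | 0.15 |
| 100% and 90% | 0.195 | 0.02 | 0.06 | 0.10 |
| 100% and 80% | 0.350 | 0.03 | 0.10 | 0.17 |

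For the planned test, r must be the correlation with change. A correlation with outcome level alone affects the baseline comparison and any post-only comparison.

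For scale, the trial is sized on an effect of 0.5, so 0.17 is about a third of it (0.17/0.5 = 0.34). With 150 students per arm (about 300/2) and class effects ignored, a two-sided 5% t-test rejects with probability 0.139 when a spurious difference of 0.10 SD is the only difference. By the same calculation, the baseline comparison would flag a baseline imbalance of 0.10 SD only about 14% of the time, so it is a weak safeguard.

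**The case against.** The strongest reply is that nothing shows families or staff knew the arm. Section 3.5 is the only section set out as a sequence, and it puts informing first. The other account is narrative: the slips go into envelopes, but their opening is not dated. Its mention of both groups may simply label the trial population. This stands. A reader might infer that students were told their own arm and then signed. The text says only that they were told about the content of the experiment and its precautions, so that stronger reading is not supported.

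Second, the change comparison cancels a stable level difference, so it would be wrong to say that nothing in section 3.10 addresses selective entry. This stands too. The figures above carry over to the planned test only if willingness is correlated with change, and the documents offer no evidence on that.

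Third, the motive for differential refusal is limited. Both arms have the same sport, lesson length, frequency and number of lessons (3.4), both wear heart-rate monitors, and 20 students from each give urine (3.3). Most exclusions are checkable facts. This makes large differences in consent less likely. It does not remove the possibility, because the load in Table 1 is set for one arm only and ability to complete is a judgement.

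None of this answers the central point: the two sections conflict, and neither closes enrolment before the arm is known.

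**Conclusion.** The point holds as a contradiction and a missing safeguard, not as demonstrated bias. Followed as written, the Participants and Grouping section allows who enters each arm to depend on the arm, and section 3.5 does not rule this out. The size of any bias is unknown. The range of about 0.01 to 0.17 SD rests on assumed consent rates, strict loss of the least willing students, and assumed correlations of 0.1 to 0.5. For the planned test, it also requires that those correlations be with change. The 14% rejection rate depends on the same conditions and should not be quoted as the trial's false-positive rate. The point is worth acting on because enrolment order decides whether randomisation protects the student comparison, and because the remedy is cheap.

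**What to change.** Rewrite Participants and Grouping and section 3.5 to one sequence:

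1. Inform all six classes with the same neutral text covering both forms of teaching.
2. Check inclusion and exclusion criteria.
3. Obtain signed consent.
4. Freeze the list of enrolled students, class by class.
5. Only then open the class envelopes, recording when and by whom.

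Report numbers approached, eligible and consenting for each class.

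This needs no extra students or visits. The cost is that teachers learn their arm later. Section 4.1 places teacher training in May-August 2024, before implementation starts in September (4.2). Training must therefore be given to all the teachers or timed after allocation. Training everyone carries some risk that elements of the experimental model reach control lessons; training later tightens the calendar.

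Much of the protocol is in the past tense, so enrolment may already be complete. In that case reordering is no longer possible. The report should then state the actual order for each class, say who knew the allocation when eligibility and consent were settled, give the same counts, compare those who consented with the full class lists where data allow, and declare any consent obtained after allocation as a limitation on the conclusion.

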3.4 Intervention Program

Both the experimental and control groups had 40-minute lessons per session, three times a week, for a total of 36 lessons. The sport practiced was volleyball.

The time allocation for the Chinese Health Physical Education curriculum model was as follows: 7 minutes for the preparation phase (1 minute for class routines, 6 minutes for warm-up activities), 30 minutes for the main phase (20 minutes for skill training, 10 minutes for physical fitness exercises), and 3 minutes for the conclusion phase (2 minutes for relaxation, 1 minute for class summary). The teaching methods for the Chinese Health Physical Education curriculum model are shown in Table 1.

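### Students are removed after class allocation for absence, incomplete tests or outside sport, and nothing in the protocol keeps them in the between-group comparison, which on the natural reading becomes per-protocol

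*Protocol*

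**What the plan says.** Protocol section 3.2 lists three grounds for removal:

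- attendance: "Criteria for removal: (1) Students absent for more than one-third of the sessions";
- tests: "2) Students who are unable to complete the tests due to personal or family reasons";
- outside sport: "3) Students who participated in other sports training sessions during the intervention, violating the intervention plan".

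A separate heading covers dropout: "Mid-study withdrawal criteria: Students who transferred schools or could not continue participating in the study due to other reasons". Removal is therefore something the researchers apply, distinct from a student leaving.

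The section on participants and grouping calls the study a randomised controlled trial, allocated by class: "Six classes of the same grade were randomly selected, with three assigned to the experimental group and the other three to the control group". Section 3.5 puts grouping before baseline testing and teaching. Section 3.4 gives the teaching schedule as "three times a week, for a total of 36 lessons".

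Section 3.10 compares the arms by independent-sample t-tests on the pre-post differences. It names no analysis set and does not say that removed students stay in.

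**The concern.** Random allocation protects a comparison only if the students compared are those who were allocated. Here, who counts is settled by what happens during the 12 weeks, and the teaching may influence it.

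- **Attendance.** Table 1 sets a minimum exercise density and a target heart rate for the experimental arm, and also asks for content that students enjoy. No load is set for the control arm. Demanding lessons could raise absence; enjoyable ones could lower it.
- **Outside sport.** A student drawn into sports training by the lessons would be removed for a possible consequence of the teaching. The protocol does not define what counts as other sports training, and the arms are visibly different to those applying the rule.
- **Tests not completed.** This also drops students on an event after allocation, and no method for handling the missing values is given.

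If removal differs by arm, in number or in kind of student, the difference in mean change mixes the teaching effect with selection. Nothing in the protocol would reveal or correct this, and the rule governs entry to every between-group comparison.

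**Working it through.** **The plan's own figures.** The protocol gives no expected removal rate, so there is no removal figure to reproduce. The scale used below is the planned effect of 0.5 SD from the sample-size paragraph. With two-sided α 0.05 and power 0.80, that effect needs 63.77, so 64 students per group; the stated 64 is reproduced on that per-group reading. The present point does not depend on it.

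**Inputs from the protocol**
- 36 lessons (section 3.4). One-third is 36 / 3 = 12, so removal starts at more than 12 missed lessons.
- About 300 students in six classes, three per arm (section 3.3): about 150 per arm.

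**Assumed inputs (not in the protocol)**
- rE and rC: fractions removed from the experimental and control arms.
- D: how far the mean change of removed students lies below that of retained students, in SD, taken as equal in both arms.

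**Formula.** Let m be the mean change of a whole arm and mR that of its retained students.

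m = (1 − r) × mR + r × (mR − D) = mR − r × D, so mR = m + r × D.

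Subtracting the arms, the comparison of retained students equals the whole-arm comparison plus

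bias = D × (rE − rC).

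**Results**

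| rE | rC | D | Bias (SD) | Share of 0.5 SD |
|---|---|---|---|---|
| 10% | 10% | any | 0 | 0% |
| 15% | 5% | 0.3 | 0.10 × 0.3 = 0.03 | 6% |
| 15% | 5% | 0.5 | 0.10 × 0.5 = 0.05 | 10% |
| 15% | 5% | 0.8 | 0.10 × 0.8 = 0.08 | 16% |
| 20% | 5% | 0.8 | 0.15 × 0.8 = 0.12 | 24% |
| 5% | 15% | 0.8 | −0.10 × 0.8 = −0.08 | −16% |

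If removed students are the better performers, D is negative and every sign reverses. If the gap differs by arm, the bias is rE × DE − rC × DC, so equal rates alone do not guarantee zero. For example, 10% in each arm with gaps of 0.5 and 0.3 gives 0.05 − 0.03 = 0.02 SD.

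**Effect on false positives.** Suppose there is no true effect, 150 students are allocated per arm, and students are treated as independent. The last assumption isolates the effect of removal and ignores allocation by class. For 15% vs 5% the retained numbers are 127.5 and 142.5, and the standard error is √(1/127.5 + 1/142.5) = 0.122 SD. Two-sided type I error is then about 5.7%, 6.9% and 10.1% for D = 0.3, 0.5 and 0.8. For 20% vs 5% with D = 0.8 it is about 16%.

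**The case against.** **The exclusion is inferred.** Section 3.2 never says that removed students' data leave the analysis. Analysis sets are often left to a SAP, and only the protocol was available here. This stands as a limit on certainty, but it does not dissolve the point. The protocol states a removal rule, and excluding the data is its natural reading. If removal also means no week-12 test, no later document can recover those data.

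**The rules are the same in both arms.** Sport, lesson length and number of lessons are also the same. This stands: if removal is alike by arm, the bias is zero.

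**A reader might infer a bias of about half the planned effect.** Removing 30% of one arm with a gap of 0.8 SD shifts that arm's mean by 0.30 × 0.8 = 0.24 SD. That is a shift in one arm. It becomes the bias in the comparison only if no student leaves the other arm, and the protocol supports neither value.

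**A reader might also infer that removal favours the experimental arm.** The document does not show this. The attendance rule may drop poor responders, while the outside-sport rule may drop better performers, so the two can offset.

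**A reader might count the inclusion rule as the same fault.** It reads "Able to complete the 12-week intervention and the three tests before the intervention, after the first intervention, and after 12 weeks of intervention". It is a prospective eligibility condition applied to both arms, and it mainly limits whom the results describe. It is not removal for observed behaviour.

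**The study also has a mechanistic aim.** Section 3.3 tracks outside activity so as to rule out other influences on metabolism. That can justify a restricted set for the 40 students giving urine. It does not justify one for the physical and mental health indicators in about 300 students.

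**Conclusion.** The point holds in a limited form. Following the protocol as written, and reading removal in its natural sense, the arms are compared after selection on events that follow allocation and that the teaching can influence. The comparison is then per-protocol in a trial described as randomised.

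The size cannot be found from the protocol. Over the unequal rates assumed above, with the experimental arm losing more of its weaker students, it is 0.03 to 0.12 SD, or 6% to 24% of the planned effect. It is zero if removal rates and the kind of student removed are alike by arm, and it reverses if the control arm loses more or if better performers are removed. The documents do not support a claim that the result is biased towards either arm; they show only that it is unprotected.

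**What to change.** 1. In section 3.10, state that the primary between-group analysis of the physical and mental health indicators keeps every consented student in the arm to which the class was allocated.
2. Seek week-12 tests from all students still in the class, whatever their attendance or outside sport.
3. Handle missing week-12 tests, whether from the second removal criterion or from withdrawal, by a stated method, such as a likelihood-based model or multiple imputation using baseline values.
4. In section 3.2, relabel the attendance and outside-sport criteria as defining a per-protocol sensitivity set. A restricted set may also be reported for the 40-student urine work.
5. Report removals by arm and reason, and attendance and outside sport by arm. The physical activity questionnaire in section 3.9 already collects much of what is needed on outside sport.

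The cost is protocol wording, a little more testing of students who are still in class, and some added analysis. The effect estimate will be somewhat diluted because low attenders are included. If teaching has already finished (section 4.2 schedules it to end by January 2025), students who were tested can still be kept in the analysis, and the missing-data method covers the rest.

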3.6 Test Indicators and Methods

The physical health indicators were tested according to the "National Physical Fitness Standards for Students (2014 Revision)," including body shape, cardiorespiratory endurance, speed, strength, flexibility, and muscular endurance. The body composition indicators were assessed using body mass index (BMI) and waist circumference. Cardiorespiratory endurance was tested using vital capacity. Strength was measured by a 1-minute sit-up test (female) or pull-up test (male). Speed was measured using the 50-meter run. Flexibility was tested using the sit-and-reach test. Muscular endurance was measured with an 800-meter run (female) or 1000-meter run (male). The main testing methods are as follows:

1) Body Mass Index (BMI): The participant stands barefoot on a height measuring platform with their back against the column, feet together, and body straight. The participant's heels, sacrum, and scapula should be in contact with the column, with the head aligned horizontally. The height is recorded in centimeters (cm), accurate to one decimal place. Weight is recorded in kilograms (kg), also accurate to one decimal place. BMI is calculated using the formula: BMI = weight / height² (kg/m²).

2) Vital Capacity: A dry, disposable mouthpiece (or disinfected non-disposable mouthpiece) is used. The participant should take a deep breath and exhale into the mouthpiece until no more air can be expelled, avoiding inhalation during the test. The final reading on the LCD screen is recorded as the vital capacity in milliliters (mL), and the maximum value is selected as the result.

3) 1-Minute Sit-Up Test (Female) / Pull-Up Test (Male): For sit-ups, the participant lies on a mat with arms crossed over their chest, palms pressed against the shoulders, and feet flat on the ground, with knees at a 90° angle. Each sit-up is counted when the elbows touch or exceed the knees. The number of sit-ups performed in 30 seconds is recorded. For pull-ups, the participant grasps a horizontal bar with both hands shoulder-width apart, hanging with straight arms. After stabilizing their body, they pull up until the chin is above the bar, and the number of successful pull-ups is recorded.

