3.8 Metabolomics Method

Forty students were randomly selected (20 from the experimental group and 20 from the control group). Urine samples (15 ml) were collected from these students before instruction, after the first session of instruction, and after 12 weeks of instruction. The samples were processed and analyzed using non-targeted metabolomics based on liquid chromatography–mass spectrometry (LC-MS) to identify differential metabolites before and after a single session of instruction, as well as before and after long-term instruction. Metabolic pathway analysis was also conducted to obtain metabolic fingerprints before and after the intervention.

Principal component analysis (PCA) and orthogonal partial least squares discriminant analysis (OPLS-DA) were employed to elucidate the differences in metabolic profiles before and after the intervention. Differential metabolites were further screened using t-tests of intragroup mean metabolite concentrations, OPLS-DA, and clustering analysis. The mass-to-charge ratios (m/z) of the metabolites were matched and analyzed against the Human Metabolome Database and the Kyoto Encyclopedia of Genes and Genomes (KEGG) database for structural identification, enrichment, and topological analysis of the differential metabolites. This approach was used to explore the metabolic pathways involved in the differential metabolites before and after a single session of instruction, as well as before and after long-term instruction, under the Healthy Physical Education Curriculum Model of China.

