3.10 Data Statistics and Analysis

Data will be analyzed using SPSS 26.0. Normality tests will be performed using the Shapiro-Wilk method, and data will be presented as mean ± standard deviation. Paired sample t-tests will be used to compare differences before and after intervention for each indicator. Independent sample t-tests will be used to compare baseline indicators between the two groups and differences between the pre- and post-intervention values. Statistical significance is set at P<0.05.

1. **Expected Timeline and Completion Dates**

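### The draw of the 40 urine donors names no class or sex strata, so the two sets of 20 are open to an avoidable chance imbalance; the expected gain from stratifying is small.

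*Protocol*

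**What the plan says.** Section 3.3 (Experiment Content) states that "40 students (20 from the experimental group and 20 from the control group) were randomly selected to provide 15 ml of urine samples". Section 3.8 (Metabolomics Method) repeats it: "Forty students were randomly selected (20 from the experimental group and 20 from the control group". Neither place mentions strata, quotas or matching.

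The students to be drawn from are described in section 3.3 as "involving six classes (approximately 300 students) who voluntarily participated". Allocation is by whole class (Participants and Grouping): "Six classes of the same grade were randomly selected, with three assigned to the experimental group and the other three to the control group".

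Both sexes take part. Section 3.6 has sex-specific tests, for example "Muscular endurance was measured with an 800-meter run (female) or 1000-meter run (male", and the exclusion criteria in section 3.2 include students who "are taking medication, or are in their menstrual period (female students".

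On analysis, section 3.8 says "Differential metabolites were further screened using t-tests of intragroup mean metabolite concentrations, OPLS-DA, and clustering analysis". Section 3.10 adds, for the indicators in general, "Independent sample t-tests will be used to compare baseline indicators between the two groups and differences between the pre- and post-intervention values". No sex term is stated in either section.

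**The concern.** The urine subsample is the smallest sample in the trial: 20 per arm out of about 150. Class is known before the draw, and sex should be just as easy to obtain. A simple random draw leaves both to chance.

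The control donors are useful because they show whether a change in metabolites belongs to the curriculum model or would also occur under conventional lessons. That calls for a comparison of change between arms. If girls and boys respond differently, or classes do, an uneven draw shifts or blurs that comparison.

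Section 3.3 also collects activity, diet and sleep data to remove other influences on the metabolites, so the plan already regards nuisance variation as a threat. How the donors are drawn cannot be repaired in a later analysis plan once the urine has been collected.

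**Working it through.** The protocol gives no calculation for the 20 + 20 donors, so there is no stated figure to reproduce.

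**Inputs.** From the protocol: about 300 students, six classes, three classes per arm, 20 donors per arm. By division: 300/2 = 150 per arm and 150/3 = 50 per class, if classes are equal. Assumed, because not given: 50% girls in each arm (40% as the alternative), and a simple random draw within arm.

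**Sex mix.** The number of girls among 20 drawn from 150 with 75 girls is hypergeometric.

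- Variance per arm = 20 × 0.5 × 0.5 × (150 − 20)/(150 − 1) = 5 × 130/149 = 4.36.
- SD of the difference between two independent arms = √(2 × 4.36) = 2.95 girls, or 2.95/20 = 14.8 percentage points.

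Exact chance of a gap at least this large:

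| Gap in girls (of 20) | 50% girls | 40% girls |
| --- | --- | --- |
| 3 or more | 39.7% | 38.7% |
| 4 or more | 23.5% | 22.5% |
| 6 or more | 6.1% | 5.6% |
| 8 or more | 1.0% | 0.9% |

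**What a gap does.** Let δ be the difference between girls and boys in mean change of a metabolite, the same in both arms. A gap of 4 girls out of 20 shifts the unadjusted between-arm difference in change by (4/20) × δ = 0.2δ. If only the level differs by sex and the change does not, δ = 0 and the shift is zero. The protocol gives no value for δ.

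**Class mix.** The three class counts (a, b, c) with a + b + c = 20 have probability C(50,a) × C(50,b) × C(50,c) / C(150,20). The expected count per class is 20/3 = 6.7.

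- Some class gives 4 or fewer donors: 39.2% in one arm; in at least one of two arms, 1 − (1 − 0.392)² = 63.0%.
- Some class gives 3 or fewer: 14.4% in one arm, 26.8% in at least one.
- Some class gives 2 or fewer: 3.7% in one arm.

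**What even class counts gain.** With intraclass correlation ρ, the variance of an arm mean is proportional to 1 + ρ(S/20 − 1), where S is the sum of the squared class counts. For 7/7/6, S = 49 + 49 + 36 = 134 and S/20 = 6.70. For the simple draw, the expected S is 145.0 and S/20 = 7.25. The protocol gives no ρ, so a range is assumed:

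- ρ = 0.02: 1.125/1.114 = 1.01, about 1% more variance under the simple draw.
- ρ = 0.20: 2.250/2.140 = 1.05, about 5% more.

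**Class as a covariate.** Each class belongs to one arm only. The three class indicators of an arm add up to the arm indicator, so with class as a fixed effect the arm effect cannot be estimated.

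**The case against.** The strongest reply is that a random draw of 20 per arm is sound as it stands and that stratifying it is a refinement. Much of that is right.

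- **Silence on strata.** A reader might infer that the protocol rules out regard for class and sex. It does not. It is silent, and a stratified draw is also a random one. What stands is that the rule appears twice, each time without strata, so its plain reading is a simple draw within arm.
- **Bias.** A reader might call the result biased. It is not; ordinary sampling error already covers chance imbalance.
- **Before-after tests.** The screening in section 3.8 is within group, in the same students, so stable sex differences largely cancel. That section describes no between-arm metabolite test. The between-group test of change in section 3.10 would also remove stable differences in level, and the section does not say whether it covers metabolites. Only a difference in response remains.
- **Class make-up.** A reader might hope that stratifying makes the arms alike in class. No draw can do that, because the arms share no class. Only the share of the three classes within an arm can be evened out.
- **Later adjustment for sex is cheap.** With 12 girls and 8 boys against 8 and 12, the correlation of sex with arm is 0.2, so the variance inflation is 1/(1 − 0.04) = 1.04. This further limits the gain from stratifying, but no sex term is stated in section 3.8 or 3.10.

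**Conclusion.** The point holds as a minor, low-cost improvement to the design. It is not an error that undermines the trial.

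Under a simple draw, about one draw in four gives a sex gap of 4 or more out of 20, while a gap of 8 or more is rare at about 1%. Some class gives 4 or fewer donors in 39% of draws within an arm, and in at least one arm 63% of the time. The cost of uneven class counts is small, about 1% to 5% in variance for an assumed intraclass correlation of 0.02 to 0.20.

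These figures rest on 150 students per arm, 50 per class, 40% to 50% girls (half girls for the rounded sex-gap figures above), and the same mix in both arms before the draw. Exclusions and refusals would change the pool. The effect on the metabolite results depends on a difference in response by sex or class, which the protocol does not give.

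**What to change.** In sections 3.3 and 3.8, state that the donors are drawn by stratified random selection from eligible, consenting students:

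- 7/7/6 across the three classes in each arm;
- as near as possible to 10 girls and 10 boys per arm, for example 4 + 3, 3 + 4 and 3 + 3 girls and boys in the three classes;
- the same sex split in both arms.

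Draw after the section 3.2 criteria have been applied, since one of them affects girls only and could upset a quota.

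State that any between-arm metabolite comparison is adjusted for sex. Do not add class as a fixed covariate. Stratifying the draw does not solve the clustering that comes from allocating whole classes; that needs its own treatment.

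If the urine has already been collected, report the sex and class make-up of each set of 20 and adjust for sex.

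The cost is slight. The number of donors and samples is unchanged, and the draw needs only class lists with sex. The protocol does not mention such lists, but schools can be assumed to hold them.
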